#### Normality Assumption Check

The normality assumptions for both primary and secondary outcomes will be checked by quantile-quantile plots. If normality fails, then the outcome variable will be taken as logarithm transformation (ie, log). We will add 0.5 to the zero-change value for either the depression or anxiety score, or the mood rating before applying the log transformation. 

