### Statistical Analysis Plan

#### Primary Analysis

Paired *t* tests will be used to detect the improvement in depression score (ie, PHQ-8) and anxiety score (ie, GAD-7) from baseline to follow-up measured 60 days later. Two-sample *t* tests will be used to examine the difference in improvements between the UR and RL groups. The mood ratings of each participant will be collected each day over the 60-day study period. We will also compare the average of daily mood rating improvements compared to baseline (ie, each consecutive daily measure minus the baseline measure) between these two groups using a longitudinal data analysis approach (eg, generalized estimating equation [GEE]). We will not compare the baseline characteristics between the samples in each arm. This practice could potentially be misleading because any differences would be due to chance [26-28].

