### Power Analysis

We will perform sample size calculation at the usual 80% power at 5% level of significance.

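### The fallback log transformation of change scores is undefined for every negative change, so it cannot be carried out as written on the primary outcomes

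*Protocol article*

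**What the plan says.** The Normality Assumption Check section of the protocol article covers all outcomes: "The normality assumptions for both primary and secondary outcomes will be checked by quantile-quantile plots". The consequence of a poor plot is fixed: "If normality fails, then the outcome variable will be taken as logarithm transformation". One adjustment comes before the log: "We will add 0.5 to the zero-change value for either the depression or anxiety score, or the mood rating". The reference to a zero change shows that the quantity being logged is the change, not the raw questionnaire score.

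The Primary Analysis section of the Statistical Analysis Plan confirms that the analysed quantities are changes. Paired t tests "will be used to detect the improvement in depression score (ie, PHQ-8) and anxiety score (ie, GAD-7) from baseline to follow-up". Two-sample "tests will be used to examine the difference in improvements between the UR and RL groups". The mood comparison uses "each consecutive daily measure minus the baseline measure". Nothing in either section deals with changes below zero.

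**The concern.** PHQ-8 change, GAD-7 change and daily mood minus baseline can each be positive, zero or negative. The rule recognises that the log fails at zero and repairs only that point, while everything below zero is left undefined. Three things are at stake once the fallback is used.

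- **The handling of negative changes becomes an unplanned choice made with the data in view.** If the analyst does nothing, the software returns missing values, and participants leave the analysis because of how they fared.
- **The null hypothesis of the paired test moves.** A mean log change of 0 corresponds to a geometric mean of exp(0) = 1 point, so the test no longer asks whether there was any change.
- **The primary analysis is affected.** The check applies to primary outcomes, including the pre-post test behind the trial's first hypothesis.

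**Working it through.** **Inputs from the protocol article.** The log rule and the 0.5 offset come from the Normality Assumption Check. The Power Analysis gives 5% significance (taken as two-sided, since the side is not stated), 80% power, d = 0.5 and 128 participants for UR versus RL. It also gives 15% dropout, stated for the secondary analyses. Allocation is 1:1 (Design).

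**Assumptions.** The SD of change is not in the document and is varied from 1 to 6 points. Change is coded so that positive means improvement. Undefined logs are lost.

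**Step 1: the plan's own figure.** Per arm, 2(1.96 + 0.84)²/0.5² = 62.7, so 63 by the normal approximation. The t-based solution is 63.8, so 64 per arm and 128 in total, as stated. With 15% dropout, 128 × 0.85 = 108.8, so 109 for the pre-post test.

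**Step 2: who has no log.** For integer change obtained by rounding a Normal(0, SD) value, P(change < 0) = Φ(−0.5/SD). This gives Φ(−0.5) = 31% at SD 1, Φ(−0.25) = 40% at SD 2, Φ(−0.1) = 46% at SD 5 and Φ(−0.083) = 47% at SD 6.

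**Step 3: paired test with no true change, n = 109.** Zeros were set to 0.5, logs taken, undefined values dropped, and a one-sample t test of log change against 0 applied. The simulation used 4,000 runs per row.

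| SD | Lost | Declares improvement | Declares worsening | Untransformed t test rejects |
|---|---|---|---|---|
| 1 | 31% | 0% | 100% | 5.6% |
| 1.5 | 37% | 0.1% | 19% | 4.8% |
| 2 | 40% | 30% | 0.1% | 4.5% |
| 3 | 43% | 99% | 0% | 5.2% |
| 4 | 45% | 100% | 0% | 4.9% |
| 5 | 46% | 100% | 0% | 4.8% |
| 6 | 47% | 100% | 0% | 4.9% |

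Two forces explain the pattern. Once negatives are gone, only values that are zero or positive remain, which pushes the mean log up. Zeros enter as log 0.5 = −0.69, which pushes it down. At a small SD the zeros dominate; from about SD 2 the positive values do.

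**Step 4: true worsening of 0.5 SD, n = 64.** Improvement is still declared in 0.5% (SD 2), 25% (SD 3), 67% (SD 4), 88% (SD 5) and 96% (SD 6) of runs.

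**Step 5: data that would plausibly trigger the fallback.** With heavy-tailed changes and no true effect (t with 3 df, scale 2.5, n = 64), false improvement is declared in 86% of runs. The untransformed t test rejects in 4.4%.

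**Step 6: RL versus UR, SD 5, 64 per arm.** When the arms have the same distribution, the log test rejects in about 4-6% of runs. With a true difference of d = 0.5 (2.5 points) and a UR mean change of 0 to 2 points, 31-46% of UR and 16-27% of RL participants are lost. Power falls from about 80% to about 25-39%.

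**The case against.** The strongest reply is that the fallback is conditional and that the article never tells anyone to delete participants. Both statements are correct. A reader might infer that the plan instructs the analyst to discard everyone who worsened. The text does not say so: it is silent on negative changes, and deletion is what software does with an undefined log. Silence does not rescue the rule, because any other handling of negatives would have to be invented after the data are seen.

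A reader might also infer that the fallback is bound to be used. The document gives no distribution of change, so this is not shown. Rounded normal data with SD 5 rarely look non-normal: in a check at n = 109, a Shapiro-Wilk test rejected in only 9% of samples. The percentages in step 3 are therefore conditional on the rule being applied. The heavy-tailed case in step 5 is closer to a triggered setting and is still serious.

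Three further limits stand:

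- **Direction depends on coding.** The Primary Analysis section speaks of improvement, but gives no formula for PHQ-8 or GAD-7. If change is follow-up minus baseline, improvers are lost and the bias points the other way.
- **The randomised comparison does not gain false positives when the arms are identical.** Its loss is power, with unequal loss of participants when the arms differ.
- **Not every outcome is affected.** The proximal outcome in the Secondary Analysis is the mood rating itself, scored 1 to 9, for which a log exists.

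A reading in which raw scores are logged would be harmless (type I error of 5.1% for the paired test in simulation). The reference to a zero change does not support that reading.

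**Conclusion.** The rule is wrong as written. It takes logs of quantities that can be negative, repairs only zero, and changes the null hypothesis of the paired test. This follows from the text alone and needs no assumption about the data.

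The size of the harm does rest on assumptions: that the fallback is triggered, that negatives drop out, that positive means improvement, and the SD of change. Under these, false improvement in the pre-post test is close to certain from SD 3 upward, about 30% at SD 2, and replaced by false worsening at SD 1-1.5 (n = 109). It would therefore overstate the case to say that the rule always produces a false improvement. For RL versus UR at SD 5 the damage is a fall in power from about 80% to about 25-39%, with type I error near 5% when the arms are identical.

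**What to change.** Delete the log fallback and the 0.5 offset from the Normality Assumption Check. Keep the stated paired and two-sample t tests on the untransformed change whatever the Q-Q plot shows, with robust or bootstrap confidence intervals. Name the signed-rank test (within person) and the rank-sum test (between arms) as sensitivity analyses. For daily mood change, keep the GEE on the untransformed scale with robust standard errors. State once how change is coded, so that the sign of every result is unambiguous. No change of primary model is needed to repair this defect. The cost is one paragraph of wording, with no effect on data collection or sample size.

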### Power Analysis

We will perform sample size calculation at the usual 80% power at 5% level of significance.

#### Primary Analysis

The Cohen methods [30] were used to calculate sample sizes for primary hypotheses. At a medium standardized effect size (ie, Cohen *d*=0.5), a total sample size of 64 is required to detect an improvement of either the depression or anxiety score from baseline to 60-day follow-up, and a sample size of 128 to detect differences between the UR and RL groups.

#### Secondary Analyses

Using the GEE-based sample size calculation method [31,32] with a small standardized effect size (ie, Cohen *d*=0.2), with the correlation coefficients of 0.2 and 0.4 among the daily mood rating improvements compared to baseline, sample sizes of 84 and 161 are required to detect a group effect for either the UR or RL group, respectively, randomly allocated at baseline. Assuming 15% of the participants will drop out before the end of the study, a sample size of 190 is required for each group.

At a small standardized effect size (ie, Cohen *d*=0.1), with a constant trend of intervention effect over days, sample sizes of 55 and 76 are required to detect the average daily causal effects of message and time window, respectively, for the UR intervention group, using the WCLS-based sample size calculation method proposed by Xu et al under the multilevel MRT design [33]. Assuming each participant has an expected 70% response rate to the sent messages and 15% of the participants are expected drop off before the end of the study, a sample size of 126 is recommended for the UR group. 

Since our primary aim is to detect differences between the UR and RL groups for depression and anxiety scores, we aimed to include at least 128 participants. However, since our goal is also to provide a service during this unprecedented COVID-19 pandemic, we will continue to make the program available and recruit participants until at least April 2021 or for as long as funding allows.

### Engagement Measures

In addition to the measures mentioned above, we will also explore measures of engagement, such as response rates to the mood messages and the BA and skills messages as well as usability data, assessed by the System Usability Scale. This will help us to improve future iterations of the texting program.

### Compensation

Participants will receive no compensation for participation in the baseline part of the study. They will receive US $20 for completion of the 60-day follow-up questionnaire.

### Data Statement

We will submit study results for publication in peer-reviewed journals and for presentations at national and international meetings. We will aim to publish all findings in open access journals when possible or in other journals with a concurrent uploading of the manuscript content into PubMed Central for public access. Curated technical appendices, statistical code, and anonymized data will become freely available from the corresponding author upon request.

### Potential Harms

Participants will be instructed to contact the researchers if their phones are lost or stolen to ensure that we stop sending messages to them. Our study website will serve as the way to control which participants receive messages and when. The server receiving data from participants (ie, text responses) is hosted behind a UC San Francisco firewall in a secure location subject to health care–grade security measures, including strict firewalls, intrusion detection, and active monitoring by study and university staff.

### Ethics and Dissemination

The informed consent form for this study can be found in Multimedia Appendix 1. All protocol amendments will be communicated for approval to the UC Berkeley Committee for the Protection of Human Subjects (CPHS). We will ensure that our text messaging content is publicly available through a Creative Commons licensing agreement. The HealthySMS system is available for use upon request.

## Results

The UC Berkeley CPHS approved this protocol in April 2020 (No. 2020-04-13162) and the trial was registered at ClinicalTrials.gov (NCT04473599). Our enrollment started on April 17, 2020, and will continue to April 2021. As of August 24, 2020, we have enrolled 229 participants, of whom 218 were English speaking and 11 were Spanish speaking.

## Discussion

### Overview

The COVID-19 pandemic and the measures taken to combat it, such as social distancing, can take a large toll on mental health, exacerbating stress and symptoms of anxiety and depression. This study aims to assess the effect of a text messaging tool for improving mental health by providing daily text messages based on BA and skill building. We expect the text messages sent to all participants in this study to improve participant well-being, as measured by depression, anxiety symptoms, and daily mood ratings, by encouraging healthy behaviors and improving coping skills.

The COVID-19 pandemic has demonstrated the need for affordable, scalable, and effective digital mental health tools [8]. Here, we provide such a tool to a wide group of individuals and examine its effectiveness.

In addition to the primary study outcome of mental health, we will also be able to assess the feasibility and challenges of deploying a large-scale public health text messaging intervention completely remotely. The COVID-19 pandemic and measures to combat the spread of the virus led to the necessity to conduct many operations online, including research. Online surveys, online consent forms, virtual online recruitment strategies, and mobile or internet interventions and programs are crucial during this time.

This study will provide important insights and practical tools on remote recruitment with English and Spanish speakers in the United States. This will also allow us to write and disseminate guidelines for other researchers in this space. Knowledge on the careful implementation of user-centered programs is now more important than ever.

Of note, our recruitment up to this point has been significantly slower for Spanish-speaking participants. Previous work also reported that recruiting Hispanics or Latinxs who speak little or no English into randomized trials is challenging [34], and online recruitment may be even more difficult because of digital literacy issues. We hope to increase the recruitment rate of our monolingual Spanish-speaking population by continuously improving the personalization of our ads on websites, such as Facebook, which has been identified as an effective strategy for online recruitment with Spanish speakers [35].

One advantage of text messaging–based interventions is the ability to easily incorporate machine learning algorithms into the research design and test whether this approach improves effectiveness. RL algorithms have the potential to greatly contribute to the effectiveness of digital mental health studies as well as to the personalization and tailoring of these studies [36,37].

Though there is a tremendous interest in the use of machine learning techniques to improve mobile health interventions, not many studies have examined the feasibility and effectiveness of these approaches. Our unique design allows us to assess the added benefit of using RL on participant outcomes, as opposed to a random messaging schedule. While the microrandomized UR group facilitates the estimation of causal effects, the participants of that group do not benefit from that knowledge. In contrast, the participants of the RL arm get allocated to empirically better-performing messages with higher probabilities as the trial progresses and new knowledge accrues. Thus, the RL arm is an outcome-adaptive MRT design, which learns online, with the randomization probability of the intervention messages being adjusted according to the participant’s responses. This design is more participant-centric than the standard MRT, which learns offline, with equal and fixed randomization probabilities over the study period. Thus, a comparison of UR versus RL arms is a comparison between these two design approaches.

Additionally, MRTs are a novel and currently underutilized study design. Typical MRTs consider binary-level components (ie, control versus intervention); however, in this study, we instead use a unique multilevel MRT design, where there are more than two levels for the intervention [33]. This study will, thus, also provide various methodological contributions, especially to the digital health literature. Results from the MRT design will allow us to optimize our text messaging intervention and serve as preliminary evidence for a just-in-time adaptive intervention (JITAI). A JITAI is a type of personalized intervention that aims to provide the right type and amount of support at the right time and is adapted to an individual’s state [38]. This will be relevant information for optimizing this text messaging stress prevention app. 

### Limitations

There are disadvantages to fully online recruitment. For instance, participants may perceive a lack of connection to the research without contact with the researcher and, therefore, show lower engagement [39]. Furthermore, online recruitment comes with risks of fraudulent activity. In addition, our monetary incentive may lead to a selection of a sample mostly motivated by financial incentives. We aimed to minimize this potential bias by only providing the reimbursement at the end of the study. We also aimed to design a messaging bank with content relevant for a broad demographic group. Thus, the content might not be adequately tailored toward specific subgroups (eg, people with chronic physical diseases or severe mental illness). Finally, we use a multilevel MRT design as opposed to contrasting sending a message with not sending a message, which is a more common design. However, by using this design, we will not be able to assess the pooled effectiveness of sending any message versus no message.

### Conclusions

This study will examine whether automated supportive text messages will improve depression, anxiety, and mood of a broad community sample in a fully remote trial. In addition, we will assess whether using an RL algorithm to personalize messages is more effective than randomly selected messages. Overall, results will contribute to our knowledge of effective psychological tools to alleviate the negative effects of social distancing.

## Appendix

Multimedia Appendix 1 Informed consent form.

## Abbreviations

BA: behavioral activation
CPHS: Committee for the Protection of Human Subjects
GAD-7: 7-item Generalized Anxiety Disorder
GEE: generalized estimating equation
HIPAA: Health Insurance Portability and Accountability Act
JITAI: just-in-time adaptive intervention
MRT: microrandomized trial
PHQ-8: 8-item Patient Health Questionnaire
RL: reinforcement learning
SPIRIT: Standard Protocol Items: Recommendations for Interventional Trials
UC: University of California
UCD: user-centered design
UR: uniform random
WCLS: weighted and centered least squares
